### Analysis plan for feasibility and efficacy outcomes

For feasibility outcomes, recruitment and retention rates will be compared across study sites and t-tests will be used to compare overall rates between the two sites. The number and reasons for failure to complete follow-up assessments will be reported. To analyze intervention engagement, youth session attendance rates for each session, percent of parent–child activities completed per week, number of narrative materials produced per child, and parent and child attendance rates at the club open house event will be reported. Intervention fidelity rates per session will be reported, and reasons for poor fidelity will be explored. For intervention acceptability and satisfaction, we will report descriptive statistics of intervention satisfaction ratings among children and parents and the proportions of children and parents who would recommend the intervention to others.

Distributions, descriptive statistics, and missing values will be examined for all efficacy study variables. Bivariate analyses will compare the characteristics of the intervention and comparison groups using two-tailed chi-square tests for categorical variables and two-tailed t-tests for continuous variables. These results will identify imbalances between groups that will be adjusted for in multivariable analyses. All analyses will utilize an intent-to-treat approach, with each child and parent participant enrolled in the intervention site analyzed as part of the group, regardless of intervention engagement. We will compare mean changes in our primary outcome (children’s SSB intake frequency) and secondary outcomes across intervention conditions using repeated measures mixed models. Generalized estimating equations will be used to account for clustering of observations within sites. Based on the relatively small sample size, complete case analysis with comparisons with baseline data will be used to address missing data as a result of loss to follow up.

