### Efficacy outcomes

The primary outcomes, child and parent consumption of SSBs and water (frequency, type, and servings of SSBs and water consumed on a typical day in the past 7 days) will be assessed using items from the Youth Risk Behavior Surveillance Survey [30] and a validated youth food-frequency questionnaire (FFQ) [31]. Secondary outcomes (knowledge related to SBBs and water, self-efficacy to reduce SSB intake and drink water) will be assessed among children and parents using modified items from validated surveys [32, 33]. Child height, weight, and waist circumference will be measured at each assessment point using portable digital scales, stadiometers, and tape measures with the participant wearing light clothing and no shoes; measurements will be taken to 2/10^th^ of the nearest inch or pound. Body mass index will be calculated as weight (kg)/height (m^2^). Youth Risk Behavior Surveillance Survey items [30] will be used to assess children’s other dietary behaviors, such as frequency of fruit, vegetable, breakfast, and fast food consumption and intake of non-SSBs (i.e., diet drinks, water, 100 % fruit juice), and children’s physical activity and sedentary behaviors (i.e., frequency and duration of moderate-to-vigorous physical activity and screen time activities). Covariates of interest will be assessed through self-report surveys and include child and parent gender, race/ethnicity, and age; child eligibility for free/reduced priced lunch; and parental education, income, and employment status.

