### Power calculation

Our sample size calculations are based on the primary hypothesis that child participants in the intervention site will have reduced SSB intake and increased water intake than child participants in the comparison site at 2 and 6 months follow-up. Results from our pilot data indicate that B&GC children consumed an average of 7.6 servings of SSBs over the past 7 days (SD = 6.5). Assuming that youth in the comparison site will experience no change in SSB intake from baseline to follow-up, a two-sided, two-sample t-test of means with alpha = 0.05 and 80 % power indicates that enrolling 45 children per group will allow us to detect a difference of 3.9 servings of SSBs per week, a clinically meaningful difference of approximately 550–940 kcals per week depending on serving size and SSB type. To account for 20 % dropout, we will enroll 54 parent–child pairs (*N* = 108) per site, yielding a total sample size of 216 participants.

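### Adjustment covariates are picked by baseline significance tests, a screen that often misses moderate differences between the two clubs and leaves the model unfixed until the data are seen

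*Protocol article*

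**What the plan says.** In the Protocol article, the section on the analysis plan for feasibility and efficacy outcomes sets out bivariate comparisons of the two groups, "using two-tailed chi-square tests for categorical variables and two-tailed t-tests for continuous variables". The next sentence turns these tests into the rule for adjustment: "These results will identify imbalances between groups that will be adjusted for in multivariable analyses". No threshold for an imbalance is given, and no covariate is named as always included.

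The Efficacy outcomes section says "Covariates of interest will be assessed through self-report surveys" and that these "include child and parent gender, race/ethnicity, and age; child eligibility for free/reduced priced lunch; and parental education, income, and employment status". That is a list of what is measured; it does not commit the analysis to adjust for any of it.

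The section on study aim and design allocates one club to each condition. The clubs were matched on size and racial/ethnic composition only. The efficacy analysis compares mean changes between conditions with mixed models for repeated measurements.

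**The concern.** A baseline test asks whether an observed difference is larger than sampling variation would produce. Confounding depends on something else: how large the difference is, and how strongly the variable predicts the outcome. The screen can pass over a strong predictor with a moderate imbalance and admit a variable of no prognostic value.

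This matters more here than in an individually randomised trial. Allocating whole clubs, one per arm, does not balance the children within them. Lunch eligibility and parental education, income and employment were not matched. Covariate adjustment is one of the few protections available, and under this rule its content is settled only after the baseline data have been tested. Moderate prognostic differences can then stay in the effect estimate.

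**Working it through.** **Inputs.** From the Power calculation section: SD 6.5 servings per week, target difference 3.9, 45 children per group evaluable, 54 enrolled per site, "a two-sided, two-sample t-test of means with alpha = 0.05 and 80 % power". From the Efficacy outcomes section: ten candidate covariates (gender, race/ethnicity and age for child and parent make six; lunch eligibility; parental education, income and employment). Assumptions not in the document: a 0.05 threshold for the baseline tests, and correlations between covariate and intake of 0.3 to 0.5.

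**The plan's own figure.** The standardised difference is 3.9/6.5 = 0.60. A two-sample t-test with 45 per group has 80.4% power and a detectable difference of 3.88, so the stated 45 reproduces.

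**How often the screen flags a true imbalance** (two-sample t-test, 54 per site, two-sided 0.05):

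| True imbalance (SD) | Flagged | Missed |
|---|---|---|
| 0.1 | 8% | 92% |
| 0.2 | 18% | 82% |
| 0.3 | 34% | 66% |
| 0.4 | 54% | 46% |
| 0.5 | 73% | 27% |

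The standard error of an observed standardised difference is √(2/54) = 0.192, so a difference must reach about 1.98 × 0.192 = 0.38 SD to be flagged. For a binary covariate near 50% this is 1.96 × √(0.25 × 2/54) = 0.19, or 19 percentage points. A true 50% against 60% is flagged 18% of the time.

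**False flags.** With ten candidates and no true imbalance, the chance that at least one is flagged is 1 − 0.95¹⁰ = 40% if the tests are independent.

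**Residual bias, follow-up levels.** Take a true imbalance of 0.3 SD and a correlation of 0.5.

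- Never adjusting: 0.3 × 0.5 × 6.5 = 0.98 servings per week.
- Screen misses the covariate (probability 0.66): an unflagged difference is by selection a smaller one. With D normal, mean 0.3 and SD 0.192, the mean of D given |D| < 0.38 is about 0.19. The bias is 0.19 × 0.5 × 6.5, about 0.63.
- Screen flags it: the adjusted estimate has bias of about zero if the covariate effect is linear.
- Average over both: 0.66 × 0.63 = 0.42, and 0.42/3.9 = 11%.

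Simulation (8,000 runs, no treatment effect) gave 0.42 for this case. Across the combinations of imbalance 0.2 to 0.4 SD and correlation 0.3 to 0.5 that were run, it gave 0.23 to 0.42, or 6% to 11% of 3.9. Always adjusting gave about zero.

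**Residual bias, mean changes.** A covariate equally related to intake at baseline and follow-up cancels from a change. Only the difference between the two correlations contributes. With the same 0.3 SD imbalance:

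- 0.5 at both times: about 0.
- 0.4 at baseline, 0.5 at follow-up: 0.66 × 0.19 × 0.1 × 6.5, about 0.08 servings on average.
- 0.3 at baseline, 0.5 at follow-up: 0.66 × 0.19 × 0.2 × 6.5, about 0.16 on average. When the screen misses, 0.19 × 0.2 × 6.5 is about 0.25.

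Simulation of these three cases agreed: 0.00, 0.09 and 0.17 on average.

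**Type I error.** In the one-covariate simulation of follow-up levels, the test-then-adjust rule rejected in 4.2% to 5.5% of runs at nominal 5%.

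**The case against.** The strongest reply is that the planned analysis compares changes, so a covariate that shifts intake equally at each visit drops out. That stands, and it makes the likely bias small. It does not make the screen sound: a covariate such as family income may well predict response over time, and the baseline test does not ask whether it does.

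Three stronger readings are tempting, and the document supports none of them.

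- A reader might put the harm at a full serving per week, a quarter of the target. That figure (0.98) is the bias from never adjusting, in a comparison of follow-up levels. Under the rule, the average is 0.42 in that comparison and less for changes.
- A reader might infer that the trial's error rate is invalid because the model depends on the data. The simulated type I error stayed close to 5%. It covered one covariate only, so it does not exclude more, but it gives no ground for the claim.
- A reader might say the screen misses most imbalances that matter. That holds up to about 0.35 SD; at 0.4 SD more than half are flagged. The document does not define an imbalance that matters.

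The text also does not say that only flagged variables may enter the model, and a separate analysis plan could name others. It would then be replacing a stated rule, not supplying a missing detail.

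Finally, unmeasured differences between the clubs cannot be separated from the intervention by any choice of covariates. That is a larger limitation, but no reason to select measured covariates badly.

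**Conclusion.** The point holds as a fault in a stated rule. Choosing covariates by baseline tests leaves a true 0.2 to 0.3 SD difference between the clubs unadjusted in about two thirds to four fifths of cases (66% to 82%), disregards prognostic value, and leaves the model open until the data are seen.

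The demonstrated size is modest. For one covariate at 0.3 SD and correlation 0.5, the average bias is about 0.4 servings per week (11% of 3.9) for follow-up levels. For changes it is near zero, or roughly 0.1 to 0.2 servings if the covariate's correlation with intake rises by 0.1 to 0.2 between visits. Several socioeconomic variables acting in the same direction could add up. These sizes rest on the assumed 0.05 threshold, the assumed correlations and a linear covariate effect. The change should be made because the better method is inexpensive, not because the bias is shown to be large.

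**What to change.** Replace the sentence that links baseline tests to adjustment with three statements.

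1. The efficacy models adjust for a short, fixed set chosen on prognostic grounds from the covariates already collected, whatever the baseline comparison shows. An example is child age, gender, race/ethnicity, lunch eligibility and one parental socioeconomic measure.
2. Baseline intake is handled either as one of the repeated responses or as a covariate, not both. The choice needs to be explicit: with non-equivalent clubs, an analysis of change and a baseline-adjusted analysis can give different answers.
3. Baseline characteristics are reported descriptively by club, with no tests that decide the model.

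No new data are needed. The cost is a few degrees of freedom with about 90 to 108 children, which is why the set must stay short, and one decision about the model for baseline intake. The report should still say that adjustment does not remove the confounding of intervention with club.

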**Methods:**

Guided by the Social Cognitive Theory and the Social Ecological Model, the H_2_GO! intervention consists of 6 weekly sessions that target beverage knowledge, attitudes, and behaviors through youth-produced messages and narratives to reduce SSB intake and encourage water intake and parent–child activities. To reach underserved youth and families, we identified Boys & Girls Clubs (B&GC) (youth-based community centers that serve an ethnically diverse and predominantly low socioeconomic status population) as a community partner and study setting. Participants (children ages 9–12 years and their parents) will be recruited from B&GC sites in Massachusetts, USA. Intervention efficacy will be assessed through a site-randomized trial (*N* = 2 youth-based community sites, pair-matched for size and racial/ethnic composition) with 54 parent–child pairs (*N* = 108) enrolled per site (*N* = 216 total). The comparison site will carry on with usual practice. Child and parental SSB and water consumption (primary outcomes) and parent and child beverage knowledge and attitudes (secondary outcomes) will be measured via self-report surveys. Additional outcomes include children’s anthropometric data, additional dietary behaviors, and physical activity. Measures will be collected at baseline, 2 and 6 months follow-up. With an estimated 20 % dropout rate, the study will have 80 % power to detect a group difference of 3.9 servings of SSBs per week.

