## Methods

### Study aim and design

This study aims to assess the feasibility and efficacy of a community-based behavioral intervention (delivered through B&GC sites) targeting SSB and water consumption among 108 parent–child pairs (*N* = 216) through a site-randomized trial. The site-level intervention will take place at two B&GC sites that were pair-matched for size and racial/ethnic composition. One site will be randomized to receive the intervention and the other site will receive usual care. The 6-week intervention consists of weekly group-based sessions with assessments conducted at baseline, 2 and 6 months follow-up (see Fig. 1 for study design). The primary outcomes are child and parental SSB and water intake, assessed via validated survey items. Secondary outcomes include child and parental knowledge and attitudes related to SSBs. Additional outcomes include children’s anthropometrics (height, weight and waist circumference), other dietary behaviors, and physical activity. We hypothesize that child participants in the intervention site will demonstrate reduced SSB intake and increased water intake compared to participants in the comparison site at 2 and 6 months follow-up. Study protocol and procedures were approved by the Boston University Medical Center Institutional Review Board.

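### The primary outcome is defined inconsistently (four outcomes, two, or one), and neither its metric nor its visit is fixed

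*Protocol article*

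**What the plan says.** Three places give four primary outcomes, namely SSB and water intake in children and in parents:

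- Abstract, Methods: "Child and parental SSB and water consumption (primary outcomes".
- Study aim and design: "The primary outcomes are child and parental SSB and water intake, assessed via validated survey items".
- Efficacy outcomes: "The primary outcomes, child and parent consumption of SSBs and water", each measured as "frequency, type, and servings of SSBs and water consumed on a typical day in the past 7 days".

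The Power calculation section narrows this to children. It rests on a "primary hypothesis that child participants in the intervention site will have reduced SSB intake and increased water intake" at 2 and 6 months, yet its mean, SD and detectable difference are all for SSB servings per week. The hypothesis under Study aim and design also names child participants only.

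The analysis plan narrows it again, to one outcome: "We will compare mean changes in our primary outcome (children’s SSB intake frequency) and secondary outcomes across intervention conditions".

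Water is primary under Efficacy outcomes, but the same section also lists it among children's other dietary behaviours, as part of "intake of non-SSBs (i.e., diet drinks, water, 100 % fruit juice".

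**The concern.** These definitions cannot all be followed. The abstract, design and measures sections reserve the secondary tier for knowledge and for attitudes or self-efficacy. Read with the analysis plan's single primary outcome, child water, parent SSB and parent water therefore belong to no tier.

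What is at stake is which result decides the trial. The Discussion says the findings will be used to judge efficacy and, if favourable, to support dissemination. With several candidate outcomes, two visits and more than one metric, the deciding comparison could be picked after the data are seen, and a nominal 5% error rate would not describe that choice. Child water is also part of the primary hypothesis without ever having been sized.

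**Working it through.** **1. The sections side by side**

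| Section | Primary outcome(s) | Metric | Visit |
|---|---|---|---|
| Abstract; Study aim and design | Child SSB, child water, parent SSB, parent water | Not fixed for the outcome | 2 and 6 months, neither singled out |
| Efficacy outcomes | The same four | Frequency, type and servings on a typical day | Not singled out |
| Power calculation | Child SSB and child water (hypothesis); child SSB only (sizing) | Servings per week | 2 and 6 months, neither singled out |
| Analysis plan | Child SSB | Frequency | Not named |

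**2. The plan's own sample size**

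Inputs from the Power calculation section: difference 3.9 servings per week, SD 6.5, two-sided alpha 0.05, power 80%. The standardised difference is 3.9 / 6.5 = 0.6.

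- Normal approximation: n = 2 × (1.96 + 0.84)² / 0.6², which rounds up to 44 per group.
- Exact two-sample t-test: 44.6, so 45 per group, with 80.4% power at 45.

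The stated 45 is reproduced. It fits one test of child SSB at 0.05. The document gives no mean, SD or target difference for water or for any parent outcome.

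**3. Chance of at least one false positive if any listed outcome may count**

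Assumption: every test uses 0.05. For k independent tests the chance is 1 − 0.95^k.

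- k = 1: 5.0%.
- k = 2 (child SSB and child water): 1 − 0.95² = 9.75%.
- k = 4 (four outcomes, one test each): 1 − 0.95⁴ = 18.5%.
- k = 8 (four outcomes × two visits, one metric each): 1 − 0.95⁸ = 33.7%.

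The outcomes will be correlated, but the document gives no correlations. Assuming a common correlation between jointly normal test statistics (simulation, one million draws per setting):

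| Tests | 0.3 | 0.5 | 0.7 |
|---|---|---|---|
| 2 | 9.5% | 9.0% | 8.3% |
| 4 | 17.4% | 15.6% | 13.0% |
| 8 | 30.1% | 25.0% | 19.1% |

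**4. What keeping several primaries would cost**

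Using the child SSB inputs with a Bonferroni split:

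- Four tests (alpha 0.05 / 4 = 0.0125): 64 per group; power at 45 per group falls to 61.7%.
- Eight tests (alpha 0.05 / 8 = 0.00625): 73 per group; power at 45 falls to 52.0%, and the detectable difference rises to 5.0 servings per week.

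**The case against.** The strongest reply is that the analysis plan is the operative text and names one primary outcome. Read alone, it implies one or two tests, and multiplicity handling is commonly left to a statistical analysis plan. That is fair as far as it goes: the absence of a multiplicity rule is not the point here. But three other sections define the primary outcome differently in current text, and an unseen plan does not reconcile them.

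A reader might infer that the protocol prescribes eight primary tests at 0.05. It does not. Eight is four outcomes times two visits, a count the document never makes. The repeated measures mixed models could give one overall test per outcome, hence four. The 0.05 appears only in the sample-size calculation, and its use elsewhere is inferred because no split is stated. The 33.7% is an upper figure for eight tests, since the same children are seen twice, parent and child share a household, and water is the intended substitute for SSBs.

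A reader might also multiply 80% by 80% and conclude that joint power for child SSB and child water is 64%. The documents do not support this. They state no rule that both must succeed, give no inputs from which power for water could be computed, and say nothing to justify independence. What stands is narrower: water is in the primary hypothesis and was not sized.

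Finally, with one site per arm, site and intervention effects cannot be separated, so no single test is assured of its 5% level. Multiplicity is not the only threat to the error rate, and this point does not cure that one.

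**Conclusion.** The contradiction is real and should be settled before analysis. The primary outcome is four outcomes in three places, two in the hypothesis used for sizing and one in the analysis plan. The metric conflict matters as well: the trial is sized on servings per week but the analysis names frequency, and the two need not move together.

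If any of four outcomes may carry the claim, the false-positive chance is 18.5% under independence and about 13% to 17% under assumed correlations of 0.7 to 0.3. With both visits counted it is at most 33.7%, and about 19% to 30% under the same correlations. These figures rest on three assumptions: 0.05 for every test, one metric per outcome, and each test being valid at 5%. The stated 80% power applies to child SSB only.

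**What to change.** In the abstract, design, measures, power and analysis sections, state one primary outcome: the one the trial is sized on, child SSB intake in servings per week. Give it in that one metric and at one visit, 2 or 6 months, which the investigators choose and record before analysis. Test it at two-sided 0.05. Make child water, parent SSB, parent water and the other visit secondary, and remove water from the additional dietary behaviours so that it appears once.

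The change is one of wording, and it leaves the sample size as it is. The cost is that water and parent outcomes lose primary status, which the power calculation does not support in any case. Whether the registry entry also needs aligning cannot be judged from the article.

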## Discussion

Community-based and narrative-based intervention strategies hold potential for decreasing SSB consumption and associated obesity risk among youth and families, particularly among socioeconomically disadvantaged and racial/ethnic minority populations who face disproportionately high obesity rates. Findings from this study will be used to assess efficacy on reducing SSB consumption among youth and families in the USA. If efficacious, the intervention has high potential for dissemination across youth-based settings and will serve as a community-based intervention model to target SSB and water consumption and disparities in childhood obesity.

